## Abstract

**Background:**

Despite the many antihypertensive medications available, two-thirds of patients with hypertension do not achieve blood pressure control. This is thought to be due to a combination of poor patient education, poor medication adherence, and "clinical inertia." The present trial evaluates an intervention consisting of health coaching, home blood pressure monitoring, and home medication titration as a method to address these three causes of poor hypertension control.

**Discussion:**

The present study is designed to assess whether the 3-pronged approach of health coaching, home blood pressure monitoring, and home medication titration can successfully improve blood pressure, and if so, whether this effect persists beyond the period of the intervention.

**Trial Registration:**

ClinicalTrials.gov identifier: NCT01013857

## Background

Hypertension remains a leading cause of preventable death despite the availability of evidence-based treatments. Even small reductions in high blood pressure have major impacts in clinical outcomes and health care spending: a 2 mm Hg decrease in systolic blood pressure (SBP) or diastolic blood pressure (DBP) significantly reduces risk of stroke, coronary heart disease, and mortality from vascular causes [1]. In the United States, over thirty percent of adults have hypertension, yet of these, only one third achieve normal blood pressure [2,3]. The discrepancy between controlled and uncontrolled hypertensive patients is even wider among ethnic minorities and low-income populations [4].

Poor blood pressure control is frequently attributed to low rates of medication adherence. Indeed, several studies have shown that only fifty to seventy percent of patients take their blood pressure medications correctly [5]. One explanation for the high rate of non-adherence is that many patients lack an understanding of the disease and its medications. The asymptomatic nature of hypertension contributes to this lack of understanding [6]. Many patients believe that hypertension is intermittent and can be best treated with non-pharmacological therapies such as stress relief or home remedies [3].

In the traditional primary care setting, patients comprehend as little as half of what their physicians convey during the appointment [7]. Yet improved health education by itself does not improve blood pressure control or medication adherence [5]. Encouraging patients to become active participants in their care, and imparting them with the skills and confidence needed for such active participation has been shown to improve blood pressure control [8,9]. Health coaching is an innovation designed to provide patients with self-management support, arming them with the information, skills and confidence needed to become active participants in their care.

Lack of treatment intensification by clinicians may be equally, if not more, important than medication adherence in attributing to poor control in hypertensive patients. Higher rates of treatment intensification are associated with improved blood pressure control [10]. However, one study found that antihypertensive medications were increased in only thirteen percent of visits in which blood pressure was elevated [11]. In a separate study, lack of timely medication intensification (the physician factor) contributed more to poor blood pressure control than low medication adherence (the patient factor) [12]. The failure to intensify treatment when appropriate has been labeled "clinical inertia" [13].

In addition to providing patients with self-management support, health coaches, using physician-created algorithms, can relay physician advice on medication intensification to patients without a physician visit. In this way, health coaches can address both the patient and physician factors associated with poor blood pressure control.

A series of publications have shown that ambulatory blood pressures better predict cardiovascular risk compared to clinic blood pressure readings [14]. One study attempted to overcome clinical inertia by giving patients the ability to titrate their own medications based on their home blood pressure measurements [15]. At 8 weeks, patients given the option to self-monitor blood pressures and titrate medications according to an algorithm had significantly lower blood pressures compared to patients in the office-based (usual) care group who neither measured home blood pressures nor titrated their own medications. A second study evaluated home blood pressure monitoring and monthly pharmacist phone calls to reduce high blood pressure [16]. The pharmacists reported abnormal values to the patient's primary care physician (PCP) along with recommendations for a titration. The blood pressure in the intervention group was improved over the usual care group and this improvement was associated with increased modifications of treatment regimens. A third study concluded that self-monitoring was only associated with better blood pressure control when it contributed to the proactive communication of abnormal values to the clinician [8]. These studies indicate that improved blood pressure can be achieved when home blood pressure monitoring allows patients to be part of clinical decision-making.

Based on the findings cited in the previous paragraphs, the present study was designed to combine health coaching, home blood pressure monitoring, and home-titration of antihypertensive medications to overcome the tri-fold barriers of inadequate health education, poor medication adherence and clinical inertia. This study is the first to use health coaches with some or no formal clinical training in place of RNs, pharmacists, or physicians for this purpose.

## Materials/Design

### Objectives

Our study investigates whether weekly telephone coaching on home blood pressure monitoring and medication adherence results in improved blood pressure control during a 6 month coaching period. Furthermore, we aim to determine whether home-titration of antihypertensive medications further increases this benefit, and whether these effects are sustained 6 months after the coaching period has ended.

### Study Design

Hypertensive patients are randomly assigned to one of two groups:

1) Control group: Patients receive weekly health coaching phone calls on home blood pressure monitoring, medication understanding, and medication adherence.

2) Active group: Patients receive weekly health coaching phone calls on home blood pressure monitoring and medication understanding and adherence, as well as assistance with home-titration of their antihypertensive medications.

A passive control group, receiving usual care, will be evaluated by retrospective chart review upon the completion of the study.

### Ethics

Ethical approval to conduct this study has been granted by the Committee on Human Research at the University of California, San Francisco (approval number H40013-33128-01).

### Study population and site

All participants are low-income English, Spanish, Cantonese, or Vietnamese speaking patients who receive primary care at the Family Health Center in San Francisco General Hospital. The Family Health Center is a primary care clinic in a teaching hospital.

### Inclusion criteria

Patients are eligible for the study if they have a documented blood pressure greater than or equal to 145/90 on two or more separate visits in the past year. SBP must be greater or equal to 145 or DBP greater or equal to 90 on both readings. The two readings can include an elevated reading taken on the day that the patient is enrolled. Eligible patients are not required to carry a diagnosis of hypertension or be prescribed antihypertensive medications at enrollment. Patients must speak Cantonese, English, Spanish, or Vietnamese.

### Exclusion criteria

Patients are excluded from the study if they are less than 30 years of age, their most recent creatinine is greater than 1.5 mg/dl, they have class III or IV heart failure, their life expectancy is less than one year or they have reduced cognitive capacity as determined by the patient's PCP. Patients with reduced cognition are included in the study if they have a known caregiver, such as a family member, capable of assisting the patient with home blood pressure monitoring and medication titration, and speaking with the health coach each week.

### Identification and recruitment of participants

San Francisco's Department of Public Health electronic patient registry was searched for patients that: (1) are assigned to a PCP at San Francisco General Hospital's Family Health Center, (2) have a diagnosis of hypertension, (3) are greater than or equal to thirty years of age, (4) have no documented serum creatinine reading greater than 1.5 mg/dl, and (5) speak Cantonese, English, Spanish, or Vietnamese.

PCPs are given the list of their screened patients and are asked to exclude patients whom they believed would be unable to monitor their blood pressure or follow medication titration instructions due to physical or cognitive disability, psychiatric illness, or other reasons.

Additionally, patients with elevated blood pressures in the clinic are screened and recruited. Clinic staff or PCPs alert the study's health coaches if any patient has a blood pressure greater than 145/90 measured during intake. Health coaches review the chart to see if the patient met the eligibility criteria, including a blood pressure greater than 145/90 on a separate visit in the previous year. If not referred directly by the PCP, the health coach approaches the patient's PCP to see if the patient was eligible in terms of cognitive ability and life expectancy.

### Patient enrollment, training, and randomization

Eligible patients are approached by a language-concordant health coach at the time of their primary care appointment and interviewed to ensure that they: (1) plan to continue coming to the Family Health Center for the next year, (2) have a telephone, (3) are willing to check their blood pressure at least twice a week, and (4) are willing to learn how to change their blood pressure medicines from home if enrolled in the active group. If patients answer yes to all of the above, they are given IRB-approved informed consent for enrollment in the study.

Patients are given a home blood pressure monitor (Omron model HEM-711AC) and trained in its use. They are also given a calendar logbook in which to record their blood pressures and heart rates. In order to ensure comprehension, health coaches request that patients "teach back" the process of checking their blood pressure and recording the values in their logbook.

At the completion of the training and consent process, health coaches and patients learn the patient's randomly generated enrollment assignment to either the active or control group. The health coach also confirms with the patient any currently prescribed antihypertensive medications and dosages.

### Sample size calculation

Sample size calculation for detecting change in systolic blood pressure as the primary outcome used a standard deviation of 15 mm Hg was used based on prior studies that have reported standard deviations ranging from 10 to 20 mm Hg. 15 mm Hg was also the standard deviation used to calculate sample size for a recent study [17]. To be able to detect an absolute difference of at least 5 mm Hg in SBP at a 2-tailed significance level of .05, and a power of 82%, 150 participants in both groups are needed. Even allowing for a substantial drop out of 30%, there is still an 83% power to detect a true effect size of 6 mm Hg.

### Data analysis

Chi-square tests (for dichotomous and categorical variables), t-test (for continuous, normally distributed variables), and non-parametric tests (e.g., Mann-Whitney-U) will be used to compare the two groups with respect to demographic characteristics, blood pressure at the time of enrollment, number and type of medications, length of time since diagnosis of hypertension, number of clinic visits in the past 12 months, primary language, and co-morbidities. The primary outcome, change in systolic blood pressure at 6 months, will be compared between the two groups using a simple t-test against the usual null hypothesis of no difference. Analyses will be performed to assess the impact, if any, of adjusting for any differences in group characteristics using multivariate analysis of variance (MANOVA). If the unadjusted (t-test) and adjusted (analysis of variance) results differ, the analysis of variance approach will take precedence.

Secondary outcomes will include difference in diastolic blood pressure, the proportion of patients achieving BP < 140/90, and proportion of patients reporting medication side effects (mild, moderate, and severe). These will be examined as per primary outcomes. Further analyses will be conducted to look for evidence of effect modification by pre-specified subgroups: starting systolic BP (≥ 160 vs. <160), by English as primary language (Y/N), and age (< median versus ≥ median). These analyses will be reported as exploratory.

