### Outcome measures

The primary outcome is systolic blood pressure measured at 0 months (enrollment), 6 months (end of coaching intervention period) and 12 months. Secondary outcome measures include diastolic blood pressure, side effects, adverse events, and patient and provider satisfaction.

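### Baseline SBP is not fixed as a covariate in the primary analysis: the unadjusted t-test on change gives up efficiency, and the deciding analysis depends on observed imbalance and an undefined comparison of results

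*Protocol article*

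**What the plan says.** The primary comparison is in the Data analysis section of the protocol article: "The primary outcome, change in systolic blood pressure at 6 months, will be compared between the two groups using a simple t-test". The next two sentences add an adjusted analysis and rank it against the t-test. The first describes the adjustment: "Analyses will be performed to assess the impact, if any, of adjusting for any differences in group characteristics using multivariate analysis of variance (MANOVA". The second gives the rule for choosing between the two results: "If the unadjusted (t-test) and adjusted (analysis of variance) results differ, the analysis of variance approach will take precedence".

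The same section lists the characteristics on which the arms will be compared. They include "blood pressure at the time of enrollment, number and type of medications", so enrolment SBP is a candidate for adjustment. Outcome measures confirms that it is available: "The primary outcome is systolic blood pressure measured at 0 months (enrollment), 6 months (end of coaching intervention period) and 12 months".

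Inclusion criteria selects on elevated readings and adds: "The two readings can include an elevated reading taken on the day that the patient is enrolled".

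The Sample size calculation applies its SD to the change score ("Sample size calculation for detecting change in systolic blood pressure as the primary outcome used a standard deviation of 15 mm Hg") and aims to "detect an absolute difference of at least 5 mm Hg in SBP at a 2-tailed significance level of .05", with 82% power and 150 per arm.

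**The concern.** A t-test on change treats the slope of 6-month SBP on baseline SBP as exactly 1. Patients enter because of high readings, and the enrolment-day reading may be one of them, so some regression to the mean is expected and a slope below 1 is plausible. If the slope is b, a fraction 1 − b of any chance baseline difference between the arms passes into the estimated effect. At b = 0.5 that is half of it. This adds noise that a baseline covariate would remove.

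The planned adjustment does not settle the matter. Read as written, baseline SBP enters the adjusted model only if the arms are found to differ on it. No criterion is given for such a difference, or for when the two results differ. The primary result is therefore not fixed before the data are seen. MANOVA is a method for several outcomes analysed jointly; it is not the name for covariate adjustment of a single outcome.

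At stake are precision in the trial's only randomised comparison and a single, predetermined answer to its primary question.

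**Working it through.** **Inputs from the protocol article.** SD of change 15 mm Hg, difference 5 mm Hg, two-sided alpha 0.05, 150 per arm, 82% power. The dropout scenario is 30% loss (105 per arm), 6 mm Hg, 83% power (all from Sample size calculation).

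**Input not in the document.** The correlation r between baseline and 6-month SBP, or equivalently the slope b with the two SDs. These are assumptions, shown as ranges.

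**1. The plan's own figures.** The standard error is SD × √(2/n).
- 5 mm Hg, 150 per arm: 15 × √(2/150) = 1.732; 5/1.732 = 2.887; power 82.1% (noncentral t) or 82.3% (normal approximation). Stated: 82%.
- 6 mm Hg, 105 per arm: 15 × √(2/105) = 2.070; 6/2.070 = 2.898; power 82.2% or 82.6%. Stated: 83%.

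Both stated figures reproduce.

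**2. Always adjusting for baseline, equal SDs at the two visits.** With a common SD σ, var(change) = 2σ²(1 − r) and the ANCOVA residual variance is σ²(1 − r²). Their ratio is (1 + r)/2, so the residual SD is 15 × √((1 + r)/2). Powers are by noncentral t with one degree of freedom removed; n is by normal approximation.

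| r (assumed) | Residual SD | Power, 150 per arm, 5 mm Hg | Power, 105 per arm, 6 mm Hg | n per arm for 82% |
|---|---|---|---|---|
| 0.3 | 12.09 | 94.6% | 94.7% | 97 |
| 0.5 | 12.99 | 91.3% | 91.5% | 112 |
| 0.7 | 13.83 | 87.7% | 87.9% | 127 |
| 0.9 | 14.62 | 83.9% | 84.1% | 142 |
| t-test as planned | 15 | 82.1% | 82.2% | 149 |

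The lost degree of freedom alone leaves power at 82.1% to one decimal when the residual SD is still 15.

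**3. Unequal SDs.** Selection on high readings can narrow the spread at baseline. In general, var(change) = residual variance + (1 − b)² × baseline variance, so the gain depends on the slope and the baseline variance, not on r alone. Hold the SD of change at 15 (variance 225) and assume a baseline SD of 10:
- b = 0.5: residual variance 225 − 0.25 × 100 = 200, SD 14.14, ratio 200/225 = 0.89, power 86%. Here the 6-month SD is √(200 + 25) = 15 and r = 0.5 × 10/15 = 0.33. The equal-SD formula would give a ratio of (1 + 0.33)/2 = 0.67 at that r, which is too favourable.
- b = 0.7: residual variance 225 − 0.09 × 100 = 216, SD 14.70, power 84%.
- b = 1: residual variance 225, no gain.

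**4. Adjusting only after a baseline difference.** The document gives no trigger. One possible reading, p < 0.05 on baseline SBP, was simulated with 20,000 replicates per scenario, equal SDs, 150 per arm and 5 mm Hg (Monte Carlo standard error at most about 0.3 points).

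| r | t-test | Adjust if p < 0.05 | Always adjust |
|---|---|---|---|
| 0.3 | 82.4% | 83.8% | 94.5% |
| 0.5 | 81.9% | 83.0% | 90.9% |
| 0.7 | 82.6% | 83.3% | 88.0% |

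Under randomisation such a trigger fires in about 5% of trials, so the t-test decides in the other 95%. This is why the rule recovers little. With no true effect, it rejected in 3.9%, 4.7% and 4.7% of replicates.

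**The case against.** The strongest reply is that the plan is not simply unadjusted. It compares enrolment blood pressure between the arms, plans to adjust for differences, and gives the adjusted result precedence. A large chance imbalance in baseline SBP is the case that this rule is meant for. If the adjusted model always contained baseline SBP, the precedence rule would amount to ANCOVA. This stands as a correct description of the plan, and a reader who stopped at the t-test sentence would misjudge it. It does not remove the concern, because baseline SBP is in the model only on condition of an observed difference that is left undefined. The p < 0.05 trigger in the simulation is an assumption, so its figures illustrate one reading of the rule and do not describe the plan itself.

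The second reply is that the gain is uncertain. This also stands. The equal-SD formula is the favourable case, and selection on high readings can lower r without lowering the slope.

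A reader might also infer more than the document supports:

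- **That the primary test is biased or invalid.** In a randomised comparison the change-score t-test is unbiased, and its standard error already reflects chance baseline imbalance.
- **That the trial is underpowered.** The 82% and 83% reproduce for exactly the planned test. Power well below 82% appears if 15 mm Hg is read as the SD of SBP at one visit with a low correlation (68% at r = 0.3), but the Sample size calculation applies it to change. Even on that other reading, the t-test has 82% at r = 0.5 and 96% at r = 0.7.
- **That the precedence rule inflates the false-positive rate.** The simulated rule did not, and other readings cannot be tested because the document does not define them.
- **That patients without a 6-month value are mishandled.** The article does not say how they are treated, and this is commonly left to the full protocol or analysis plan.

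**Conclusion.** The concern holds in a limited form. The article names an unadjusted t-test on 6-month change as primary and leaves baseline SBP to a conditional adjustment, so neither the covariates nor the analysis that decides is fixed. This is a stated choice, not a detail left to a later document. The consequence is lost efficiency and an open primary analysis; validity is not affected.

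Under equal SDs and r from 0.9 down to 0.3, the power forgone is about 2 to 12 points. Equivalently, 82% power would need about 5% to 35% fewer patients (142 to 97 per arm against 149). With a narrower baseline SD of 10 and slope 0.5, the gain is about 4 points; at slope 1 it is zero. The document does not show which of these cases applies. The absence of a fixed covariate and of a defined precedence criterion can be read directly from the text and depends on none of these assumptions.

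**What to change.** Prespecify one primary analysis: ANCOVA of 6-month SBP (or of change, which gives the same treatment estimate once baseline is in the model) on randomised arm and baseline SBP, with baseline included whatever the observed balance. Keep the unadjusted t-test on change as a sensitivity analysis. Remove the rule that lets an adjusted result prevail when results differ, and replace the MANOVA label with the name of the model actually fitted.

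The cost is one degree of freedom and a change of wording. The data are already planned, and the sample size can stay as it is.

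### The adjusted analysis that can override the primary t-test has no fixed covariates, no criterion for when it overrides, and a name (MANOVA) that does not fit a single outcome

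*Protocol article*

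**What the plan says.** All of the rule stands in the Data analysis section of the protocol article.

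- Primary comparison: the endpoint is given as "The primary outcome, change in systolic blood pressure at 6 months". For the test, the section says that this endpoint "will be compared between the two groups using a simple t-test against the usual null hypothesis of no difference".
- Baseline tests: chi-square, t and non-parametric tests "will be used to compare the two groups with respect to demographic characteristics, blood pressure at the time of enrollment, number and type of medications", followed by time since diagnosis, recent clinic visits, language and co-morbidities.
- Adjustment: the impact of "adjusting for any differences in group characteristics using multivariate analysis of variance (MANOVA") is to be assessed.
- Precedence: "If the unadjusted (t-test) and adjusted (analysis of variance) results differ, the analysis of variance approach will take precedence".

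The secondary outcomes are to be handled in the same way as the primary one.

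The Sample size calculation section rests on a two-group comparison of means with an SD of 15 mm Hg. Its aim is stated as "To be able to detect an absolute difference of at least 5 mm Hg in SBP", while the error rates and group size are given as "2-tailed significance level of .05, and a power of 82%, 150 participants in both groups are needed".

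**The concern.** Three things in this rule are fixed badly.

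1. **Covariates follow the observed imbalance.** The groups are randomised, so a baseline difference between them arises mainly by chance and says nothing about whether the characteristic predicts 6-month SBP. Baseline SBP, the obvious covariate for a blood pressure outcome, gets in only if the groups happen to differ on it.
2. **The override has no trigger.** Results could differ in significance, in size or in direction, and the section does not say which counts. No threshold is given for a baseline difference either.
3. **The label does not fit.** MANOVA tests several outcome variables jointly. The primary outcome here is one continuous variable, for which a covariate-adjusted mean difference comes from ANCOVA.

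This is not detail left to a later analysis plan. The protocol states a rule of precedence for its primary result, and an analysis plan that fixed the model in advance would have to depart from it. At stake are the definition of the primary result, freedom to choose after the data are seen, and precision.

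**Working it through.** **Inputs.** From the Sample size calculation section: 150 per arm, difference 5 mm Hg, SD 15 mm Hg, two-sided alpha .05, stated power 82%; also 83% for 6 mm Hg after 30% dropout. Assumed, because the article gives no figure: 8 independent baseline characteristics (baseline SBP among them), entry into the model when the baseline test has p<.05, and correlation r between baseline and 6-month SBP of 0.3, 0.5 or 0.7.

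**Step 1: the stated power.** Power = Φ(δ/SE − 1.96), with SE = SD × √(2/n).
- 150 per arm: SE = 15 × √(2/150) = 1.732; 5/1.732 = 2.887; Φ(0.927) = 82.3%, against 82% stated.
- 150 × 0.7 = 105 per arm: SE = 15 × √(2/105) = 2.070; 6/2.070 = 2.898; Φ(0.938) = 82.6%, against 83% stated.

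Both figures reproduce, and both belong to the unadjusted comparison.

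**Step 2: how often a difference turns up by chance.** 1 − 0.95^8 = 1 − 0.663 = 34%. In the other 66% of trials nothing passes the assumed threshold and the t-test stands alone.

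**Step 3: the rule applied mechanically.** It was simulated with 150 per arm, an SD of change of 15, correlation of baseline SBP with the change of 0.3 to 0.6 in size, and three other characteristics weakly prognostic.

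| Quantity | Result |
|---|---|
| Type I error of the rule | 3.8% to 4.6% |
| Power of the rule at 5 mm Hg | 82% to 83.5% |
| Power of the t-test at 5 mm Hg | 82% |
| Adjusted and unadjusted analyses disagree on significance, no true effect | 1% to 2% |
| The same, true difference 5 mm Hg | about 3% |
| Type I error if the analyst may pick among unadjusted, imbalance-adjusted and baseline-adjusted models | 6.3% to 8.1% |

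**Step 4: what a covariate fixed in advance would give.** Let s be the SD of SBP, equal at both times. The change score has SD s√(2(1−r)). ANCOVA on baseline SBP has residual SD s√(1−r²). The ratio of the variances is (1−r²)/(2(1−r)) = (1+r)/2, which is 0.65, 0.75 and 0.85 for r = 0.3, 0.5 and 0.7.

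*Reading A, 15 is the SD of change.* The ANCOVA residual SD is 15√((1+r)/2).

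| r | Residual SD | SE | 5/SE | ANCOVA power | t-test power |
|---|---|---|---|---|---|
| 0.3 | 12.09 | 1.396 | 3.581 | 94.7% | 82.3% |
| 0.5 | 12.99 | 1.500 | 3.333 | 91.5% | 82.3% |
| 0.7 | 13.83 | 1.597 | 3.131 | 87.9% | 82.3% |

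Simulation gave about 95%, 90% and 87% for ANCOVA and about 82% for the rule, within about 1.5 points of the formula.

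*Reading B, 15 is the SD of SBP itself.* The change score has SD 15√(2(1−r)) and ANCOVA has 15√(1−r²).

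| r | SD of change | t-test power | Rule, simulated | ANCOVA SD | ANCOVA power | ANCOVA, simulated |
|---|---|---|---|---|---|---|
| 0.3 | 17.75 | 68.4% | 70% | 14.31 | 85.7% | 85% |
| 0.5 | 15.00 | 82.3% | 84% | 12.99 | 91.5% | 92% |
| 0.7 | 11.62 | 96.1% | 96% | 10.71 | 98.1% | 98% |

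Under both readings the rule sits close to the t-test, and the fixed ANCOVA lies above both.

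**The case against.** The strongest reply is that little goes wrong if the rule is followed mechanically. Type I error is at or below nominal, power matches the planned test, and the two analyses seldom reach different verdicts. The candidate characteristics and the order of precedence are stated in advance. MANOVA is probably a loose name for a covariate-adjusted analysis of variance, since the next sentence uses that plainer term. All of this stands, and it limits the severity.

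Four stronger readings are tempting, and the documents do not support them.

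- *The rule costs power.* A reader might set 70% against 85% (reading B, r = 0.3) and blame the rule. The gap is between a change score and ANCOVA, and it would remain if the precedence rule were deleted and the t-test kept. The 70% also needs 15 to be the SD of SBP itself, although the Sample size calculation section introduces that SD for detecting change.
- *The rule inflates type I error.* The 6.3% to 8.1% applies to an analyst who chooses freely among three models. The section fixes which of the two analyses wins, so this measures what the gaps in its wording could allow, not the stated rule.
- *The primary result always comes from a data-chosen model.* Under the assumed threshold, about two trials in three would have no difference to adjust for. For the same reason, sizing the trial on the t-test has little practical effect.
- *Undiagnosed patients drop out of the decisive analysis.* The Inclusion criteria say "Eligible patients are not required to carry a diagnosis of hypertension or be prescribed antihypertensive medications at enrollment", and time since diagnosis is among the tested characteristics. But a loss would require that variable to differ by arm, to enter the model, and to be treated as missing for these patients. The article states no complete-case rule, so this is speculation.

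What the reply does not answer is that the threshold, the covariates and the meaning of a difference in results are all unstated, so a mechanical reading has to be supplied by the reader.

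**Conclusion.** The point holds as a should-fix. The protocol lets an analysis with unspecified covariates and a misfitting name override its primary t-test on an undefined trigger. The damage is an undefined decisive model, room for choice after the data are seen, and precision left unused. It is not an inflated error rate or a loss of power against the planned test.

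The precision forgone is the only part with a size. At 150 per arm and 5 mm Hg, fixing baseline SBP raises power from about 82% to between 87% and 95% if 15 is the SD of change. If 15 is the SD of SBP, it raises power from about 70%, 84% and 96% to 85%, 92% and 98% at r = 0.3, 0.5 and 0.7. The gain shrinks as the correlation rises. The article gives no correlation, number of characteristics or selection threshold, so these are ranges under assumptions.

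**What to change.** In the Data analysis section:

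- Name one primary analysis: ANCOVA of 6-month SBP on arm with baseline SBP as covariate, plus at most a few others named now that every patient has, such as age and primary language.
- Delete the precedence rule and the adjustment for observed differences.
- Replace MANOVA with ANCOVA.
- Keep the unadjusted t-test as a sensitivity analysis.
- Carry the same model form to diastolic pressure, since the secondary outcomes follow the primary one.

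The cost is a few sentences and no new data, because SBP at enrolment is already collected. The trial gives up adjusting for chance imbalances as its primary result; such an analysis can still be reported as supportive. The change should be made before outcome data are compared by arm.

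### Effect modification by starting systolic BP and by age is examined only through two-group splits, which costs power if the gradient is roughly linear; continuous interaction terms would be a cheap gain

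*Protocol article*

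**What the plan says.** The protocol article, Data analysis, states: "Further analyses will be conducted to look for evidence of effect modification by pre-specified subgroups". Three modifiers follow: "starting systolic BP (≥ 160 vs. <160"), "by English as primary language (Y/N"), and "age (< median versus ≥ median"). On their status it says: "These analyses will be reported as exploratory".

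Language is coded as a yes/no variable and is not at issue. Starting SBP and age are continuous, but the article defines them for this purpose only as two groups. It names no continuous interaction and gives no reason for either cut. It also reports no distribution for baseline SBP or age.

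**The concern.** An interaction contrast is much less precise than a main effect in the same trial. This trial is sized for a 5 mm Hg main effect, so any subgroup question starts with little power. Cutting a continuous modifier in two weakens it further: a patient at 159 mm Hg is separated from one at 161, while patients at 161 and 200 are treated alike.

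What is at stake is how a null subgroup result reads. If the benefit of home titration rises steadily with starting SBP or changes steadily with age, the split is more likely to miss it than a continuous term fitted to the same data. No primary or secondary conclusion depends on this.

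**Working it through.** **Inputs from the article (Sample size calculation).** Outcome SD 15 mm Hg ("used a standard deviation of 15 mm Hg was used based on prior studies", which reported SDs of 10 to 20); the main comparison is meant to "detect an absolute difference of at least 5 mm Hg in SBP at a 2-tailed significance level of .05", with "a power of 82%, 150 participants in both groups are needed". The same section considers 30% dropout, which leaves 210 of 300.

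**Reproducing the plan's own figures.** Power = Φ(d / [SD × √(2/n)] − 1.96).
- n = 150 per group, d = 5: SE = 15 × √(2/150) = 1.73 and power = 82.3% (stated 82%).
- n = 105 per group, d = 6: SE = 15 × √(2/105) = 2.07 and power = 82.6% (stated 83%).

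Both agree, so SD 15 is a fair basis for what follows. The article states no power for the subgroup analyses.

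**Information kept by a split.** If the interaction is linear, the share kept is the squared correlation between the modifier and its two-group version. For a normal modifier cut at standardised value z with a proportion p above the cut, this is φ(z)² / [p(1−p)].

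*Age at the median (distribution assumed).* Here z = 0 and p = 0.5, so the share kept is 2/π = 0.637, a loss of 36%. In information terms, 300 patients act like 300 × 0.637 = 191. Other shapes:

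| Assumed age distribution | Loss |
|---|---|
| Normal (mean 60, SD 12), truncated at 30 | 36% |
| Uniform, 30 to 85 | 25% |
| Exponential | 52% |

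*Starting SBP at 160 (mean and SD assumed).* Entry requires SBP of at least 145 or DBP of at least 90, so some patients may have SBP below 145. The table therefore shows the result with and without truncation at 145.

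| Assumed mean, SD | Truncated at 145? | Share above 160 | Information kept | Loss |
|---|---|---|---|---|
| 150, 15 | No | 25% | 0.54 | 46% |
| 155, 15 | No | 37% | 0.61 | 39% |
| 150, 15 | Yes | 40% | 0.67 | 33% |
| 155, 15 | Yes | 49% | 0.65 | 35% |

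Over a wider grid (mean 145 to 165, SD 10 to 20) the loss is about 32% to 50% with truncation and 36% to 73% without. The 73% comes from one corner (mean 145, SD 10), where only about 7% of patients would lie above 160.

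**Power for the age interaction.** With equal halves there are N/4 patients in each of four cells, so the SE of the difference in effect is SD × √[4/(N/4)].
- N = 300: 15 × √(4/75) = 3.46 mm Hg. Detectable with 80% power: (1.96 + 0.84) × 3.46 = 9.7 mm Hg.
- N = 210: 15 × √(4/52.5) = 4.14 mm Hg. Detectable with 80% power: 11.6 mm Hg.

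Let d be the difference in effect between the halves. Power with the split is Φ(d/SE − 1.96). With a continuous term, a normal modifier and a linear gradient, it is Φ(d/[SE × √(2/π)] − 1.96).

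| N | SD | d (mm Hg) | Split | Continuous |
|---|---|---|---|---|
| 300 | 15 | 5 | 30% | 44% |
| 300 | 15 | 8 | 64% | 82.5% |
| 210 | 15 | 5 | 23% | 33% |
| 210 | 15 | 8 | 49% | 68% |
| 300 | 10 | 5 | 58% | 77% |
| 300 | 20 | 5 | 19% | 27% |

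**Two checks in the plan's favour (simulation, N = 300, SD 15, age normal with mean 60 and SD 12).**
- Type I error with the sample-median split was 0.051, against 0.050 with continuous age.
- With a true step of 9.7 mm Hg at age 60, the split had 75% power and the linear term 58%.

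**The case against.** The article contains no error or contradiction here. The subgroups are named in advance and labelled exploratory, a display by subgroup is conventional, and no model is specified, so a fuller analysis plan might add a continuous term. This stands as a limit on the weight of the point. It does not remove it, because the article does state the two-group form for both variables.

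Three stronger readings are tempting, and the article does not support them.

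- **The split has no benefit.** It does. It is easier to present, and it has more power than a linear term if the effect changes in a step at the cut.
- **A median known only after enrolment undermines pre-specification or biases the test.** The rule is fixed in advance. It depends on baseline age and not on outcomes, so it leaves no room to choose a convenient cut. Type I error is not inflated, and the groups are balanced by construction. A fixed age cut would trade that balance for a stable definition, which is no clear gain when the age distribution is unknown.
- **More than a third of the information is lost for both variables.** The 2/π figure belongs to a median split of a normal variable. The loss can be 25% for uniform age, and it is 33% to 35% for the 160 cut after truncation at 145. Markedly unequal SBP groups do not follow from the article either: with truncation, 40% to 49% lie above 160 under the assumptions shown.

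It is also fair to say that at SD 15 neither method is well powered for a 5 mm Hg interaction. That supports keeping the exploratory label. It is not a reason to prefer the less efficient test.

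**Conclusion.** The point holds as a minor improvement in precision. Under a roughly linear gradient, the planned splits typically give up about a quarter to a half of the information on the interaction, and at SD 15 about 10 to 19 percentage points of power in the age cases worked above. These sizes rest on assumed modifier distributions, on linearity and, for the power figures, on equal halves and the outcome SD in the article. If the true modification is a step at the chosen cut, the comparison reverses. The primary analysis and the validity of the subgroup tests are not affected.

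**What to change.** In Data analysis, make the exploratory test of effect modification the treatment-by-baseline-SBP and treatment-by-age interactions, with both variables continuous, in the model for the 6-month SBP outcome. Keep the estimates for the 160 mm Hg groups and the median-age groups as a descriptive display, which also shows whether a linear gradient is reasonable. Leave the language subgroup, the median rule and the exploratory label as they are.

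The cost is a sentence or two of wording, with no extra patients, visits or data. The one downside is the assumed linear gradient: a step effect at the cut would be picked up less well by the continuous term, and the retained display is the safeguard against overlooking it.
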